### Intervention Development

#### Youth Advisory Boards

Consistent with the model of community-based participatory research [50,51] and requirements for all ATN studies, YABs reviewed and provided feedback on all study protocols and interventions before study launch and are involved on an ongoing basis to ensure that interventions are continuously improved. In particular, YABs reviewed and provided feedback on adaptations or cutting of every text message in the libraries of existing text messages (details below). YABs also provide topics of interest for peer support discussion boards and its associated website content and branding. YABs comprise about 10 seronegative YAHR and youth living with HIV (undisclosed) in both Los Angeles and New Orleans and reflect the diversity of the youth in both cities.

#### Text-Message Libraries

The existing libraries of HIV prevention messages adapted by the YAB include: (1) Project Tech Support [52], which has developed over 600 theory-based text messages specifically for methamphetamine-using MSM focused on reducing sexual risk behaviors and methamphetamine use and increasing ART use and adherence for those who are living with HIV; (2) the UCARE4LIFE text-message library from the Health Resources & Services Administration HIV/AIDS Bureau [53], which were designed for youth living with HIV but adapted for YAHR for this study; and (3) the PrEPTech library from youth+tech+health focused on increasing uptake and adherence to PrEP [54]. These libraries formed the basis of the initial text-message content for adaptation in collaboration with the YABs. Message libraries have been tailored for 2 different risk profiles—LGBTQ and heterosexually identified youth. Research indicates that messaging interventions based on cognitive behavioral theory are more likely to be successful [52,55-57]. In particular, text-message libraries from Project Tech Support [52], which form the majority of messages adopted for this project, were based on Social Support Theory [58-60], the Health Belief Model [61-63], and Social Cognitive Theory [64,65].

### Intervention Conditions to Optimize the HIV Prevention Continuum

#### Condition A/Arm 1: Automated Text-Messaging and Monitoring Alone

AMM is a relatively low-cost and scalable intervention that could be diffused nationally. AMM is provided to all study participants across study arms as part of the enhanced standard of care and ethical requirement to provide prevention information to high-risk youth per ATN guidelines.

##### Daily Texts to Inform, Motivate, and Refer Youth to Services

Messages are sent daily, at times selected by each participant. Some evidence suggests that several text messages each day might be required to have an impact on behavioral outcomes [66-68]; therefore, up to 5 messages are sent per day in 5 content streams outlined in Table 1. Participants may opt-out of and opt-in to each of the 5 message streams at any time during the study by contacting interviewers and by updating preferences at each follow-up assessment when interviewers prompt participants and collect feedback on message experience. If a participant texts *STOP*, the SMS gateway provider (Twilio) stops sending all text messages. Messages are sent every day on health care (eg, medical, dental, and provider interactions), wellness (eg, mental health, diet and physical activity, social support, housing, jobs, and education), and medication reminders (if taking). Messages on sexual health and substance use are sent on Thursdays, Fridays, and Saturdays, a design decision based on YAB guidance to minimize messaging burden for these sensitive topics while maximizing impact on days when risk behaviors are most likely.

**Table 1 table1:** Automated text-messaging and monitoring intervention daily text message examples.

Text message type and Risk Profile: MSM^a^		Risk Profile: non-MSM
**Health care (70 messages)**		
	Your health is important.	First things first. Are you doing everything you can to stay healthy?
	Vaccinations can be injections, drops or sprays. They are a proven way to prevent disease and keep you healthy.	It's your life we're talking about. Be a part of EVERY decision about your health care.
	New in the area? Make sure to get a new doctor close by! Go to http://tinyurl.com/js8mqa6 to find free clinics close to you.	Get nervous talking to your provider? Write down any questions you have and bring them with you so you don’t forget.
**Wellness (70 messages)**		
	Friends can be good medicine. If you need to talk, give a friend a call.	Have you laughed today? Laughing is a great form of stress-relief, get some laughs in your day!
	Gay Pride is taking care of yourself.	It's OK to ask for help.
	Been inside all day? Get outside and soak up some quick sun for a boost of energy.	A budget can help make sure you have enough money every month. To learn more, visit http://tinyurl.com/kx8bxp2
**Sexual health (100 messages)**		
	If your partner wants to get tested for HIV, text KNOWIT (566948) and enter their ZIP code. KNOWIT will text back a nearby testing site.	Left untreated, some STIs can cause health problems that make it hard or impossible for a woman to get pregnant. Visit http://1.usa.gov/1dm9P0B to learn more.
	Open relationship? Know your boundaries.	Make sure the only thing you “get” is laid.
	Friction is the enemy. You can lube up every time.	Myth: Women can’t give men HIV; Fact: Both men and women can get HIV from vaginal and anal sex.
**Substance use (90 messages)**		
	Stay in control—people who are drunk or high take more risks.	When was the last time you had sex sober?
	Drinking alcohol can take a toll on your body. Take care of you!	Only take a fixed amount of cash out (and no cards) if you want to control how much you drink.
	Spending too much money on Tina?	Going out tonight? Be safe. Party smart.
**Medication adherence (100 messages)**		
	Reminder. It's going to be a great day.	It's that time again.
	When you take your meds regularly, you're in control.	Take care of yourself today.
	Is your stomach feeling a little off after taking your PrEP? Try taking your pill with food to ease possible stomach discomfort.	Where are you storing your PrEP? Your hot car or fridge can damage the medication-- keep it at room temperature.

^a^MSM: men who have sex with men.

##### Weekly Monitoring

In addition to monitoring for HIV/STI symptoms for follow-up testing and linkage as described above for study assessments, monitoring also functions as self-monitoring. Self-monitoring is a key skill for self-management and a core construct in social cognitive theories [69-71]. Preliminary studies on mobile self-monitoring demonstrated feasibility and acceptability [72,73], validity and reliability [74,75], compliance (ie, protocol adherence) [76], and user preferences. The efficacy of theory-based mobile self-monitoring to support self-directed self-management has also been demonstrated [74,77-80]. Self-monitoring by mobile or Web apps to support motivational interviewing to reduce substance use and sexual risk has demonstrated efficacy with substance users, persons living with HIV, and persons at high-risk for HIV infection [81-86]. In this study, weekly text-messaging monitoring surveys remain open for response for 48 hours. In the cases of nonresponse, CommCare automatically sends a follow-up prompt 24 hours after the initial prompt. After 2 weeks of nonresponse, interviewers initiate follow-up to assess current status of the youth. If participants are nonresponsive to text messages or opted-out via the SMS gateway by texting STOP, emails are sent instead with a weblink to a RedCap version of the survey.

#### Condition B/Arm 2: Automated Text-Messaging and Monitoring and Online Peer Support Groups Via Private Social Media

Peer Support groups are a low-cost strategy to enhance prevention and adherence interventions. Relationships have been shown to be motivating and increase engagement and retention in care for a range of chronic diseases [87-89]. Adolescence, in particular, is a developmental period where the influence of peers is crucial [90]. Almost every EBI for HIV prevention in the CDC’s Compendium of EBI has a peer support component [91]. Several studies or online peer support groups with young minority MSM and LGBTQ youth have demonstrated preliminary efficacy for reducing HIV risks [92-94]. In addition, 2 other online peer support group interventions combined with peer paraprofessional coaches via private Facebook groups (no longer feasible because of privacy and IRB concerns) found increased requests by MSM for HIV home test kits in Los Angeles [95] and increased clinic-based HIV testing in Peru [96]. Although a recent meta-analysis of 31 RCTs did not find significant benefits for electronic peer-to-peer interventions alone [97], the review noted that studies combining peer support with other interventions found some evidence for efficacy on the basis of associations between greater use of peer support via social media, indicating a dose-response association [98-100]. Therefore, this study is examining online peer support groups, moderated by paraprofessional near-peer coaches, in conjunction with AMM and also in conjunction with coaching in study Condition D/Arm 4.

Participants randomized to online peer support groups (Conditions B/Arm 2 and D/Arm 4) are invited to participate in a private Web discussion board hosted on Muut. Muut is an open-source discussion platform that is mobile- and desktop-friendly. Users can personalize their Muut profiles using avatars and photos, and content created can be continually reorganized according to new and relevant *channels* (eg, for a PrEP channel and mental health-related channels). Muut includes social media features such as *likes* and emojis, and multimedia content by embedding the forums in the study website. Private messaging functions are disabled because of IRB concerns around communication among participants that cannot be monitored or moderated. Participants are required to register and request access to join, which is facilitated by detailed screenshot instructions sent by SMS and in-person by coaches at the recruitment sites. Coaches and project coordinators review access requests to ensure that only study participants are attempting to join the forums and that their usernames do not compromise their anonymity by including their names. In total, 2 forums are available, 1 for LGBTQ-identified youth and another for heterosexual-identified youth.

Coaches and intervention coordinators seed discussions by creating and posting blogs, polls, and discussion topics twice a week on popular culture and general health and wellness to increase engagement (on the basis of YAB feedback), in addition to HIV prevention continuum themes (health care, PrEP, PEP, condom use, STIs, and HIV) and secondary outcome themes (mental health, substance use, and housing), including referral, resource, and services information. Coaches and coordinators also moderate the forums throughout each day to ensure that ground rules are followed, delete inappropriate posts, post correct information, and engage with and reward participant-initiated content. Participants are given warnings and removed from the discussion board if they post inappropriate content 3 times after receiving feedback for each occurrence, which includes: solicitations for sex and drug use; racist, homophobic, or other stigmatizing content; pornographic content; *trolling* inflammatory remarks or personal insults.

Participants are incentivized to participate and support their peers by posting questions and new discussion threads and responding to content posted by peers and coaches, such as sharing experiences and advice. Participants receive US $10 in cash or electronic transfer for initiating or responding to posts 3 times in a week, for up to 16 weeks over follow-up period.

#### Condition C/Arm 3: Automated Text-Messaging and Monitoring and Coaching—Strengths-Based, Youth-Centered

There are 2 levels of coaching engagement and overall functions in this intervention condition anticipating youths’ varying preferences and needs over time; patient navigation (ie, services and resource referral and linkage) and more intensive, strengths-based, youth-centered, goal-focused coaching. *Patient Navigators* are one of the primary strategies advocated to link and retain high-risk populations to prevention and treatment services. Similar to navigators used for chronic diseases [101-103], the CDC recommends that patient navigators can help optimize the HIV prevention continuum [104,105]. Patient navigation involves a paraprofessional or experienced peer helping persons link to health care and services, assist with insurance, problem solve barriers to care, and provide supportive counseling and follow-up to motivate engagement and retention in health and prevention services. Coaching is based on the strengths-based model [106], which has demonstrated positive impact with homeless youth [107] and persons living with HIV [108]. Critical components of the model include identifying personal and interpersonal strengths rather than deficits and then setting, problem-solving, and accomplishing long- and short-term client-centered goals selected by participants in collaboration with coaches with a focus on hierarchies of needs (housing, food, and employment) as well as programmatic priorities.

In this study, coaching formally begins with a strengths-based assessment, an approximately 45-min open-ended interview that addresses 6 life domains: (1) daily living (survival needs such as food, housing, finances, and employment); (2) physical health (non-HIV related health problems); (3) health care; (4) social relationships (including social support, disclosure, and stigma); (5) mental health; and (6) HIV risks (substance use and risky sexual behaviors). Youth are asked to identify their current status within each domain, as well as strengths and challenges in each area. This assessment guides the development of personalized goals. Each youth has a maximum of 3 goals at any given time. The coach and youth identify a primary goal to address following the session including identification of resources and skills needed to achieve the goal (eg, problem-solving and coping skills). Typically, long-term or lofty goals must be broken down into smaller short-term *SMART* goals (ie, specific, measurable, achievable, realistic, and timely). Responsibility for goals is shared among the youth and coach depending on the nature of the goals. At each subsequent session, the coach *checks in* with the youth on goals set in previous sessions. As goals are accomplished, new goals are set. Goals not met are problem solved and adjusted to be achievable in successive approximation.

Coaches focus on the following priorities in their contact with youth:

Crisis support to address youths’ immediate priorities and needs, particularly housing, which are typical barriers to engaging in other health-promoting activitiesCompletion of a strengths-based assessment session, including goal settingProblem-solving priorities and facilitating linkages to prevention services, health care, and other services and providers (eg, Case Managers at recruitment sites, nearby agencies, or providers for mental health, substance abuse, housing, jobs, school, in conjunction with Case Managers, if available)Appointment coordination, scheduling, and remindersFollow up with clients to give a rewarding message for attending appointments (eg, Great job attending your appointment!) or to problem solve barriers if patient missed an appointment

Although the ultimate aim of this study’s coaching intervention is to improve HIV prevention continuum, coaches also aim to address the hierarchy of needs and secondary outcomes that are hypothesized to influence prevention outcomes, such as homelessness, employment, mental health, and substance abuse. More details on the coaching intervention are provided in a publication for a sister protocol for youth living with HIV [47].

Coaching represents the most intensive person-mediated strategy in this study; however, coaches use a variety of means of communication and interaction on the basis of participant preferences and responsiveness. These include text messaging, phone calls, social media private messaging, video chat, email, and in-person contacts. In particular, in-person contacts are accommodated to meet youths’ preferences for initiating a coaching relationship and building trust and rapport, including on an ad hoc basis at recruitment sites with coaches being on site to engage participants who are nonresponsive to initial text message and telephone contacts.

Importantly, and as noted in the introduction, this is not a manualized or scripted intervention. Instead, it is based on training, monitoring, and supervision using common practice elements or skills identified across EBIs for youth prevention and behavioral health [109,110], in addition to the priority topic domains of the project. The practice elements used are engagement/rapport building (including setting expectations), goal setting, problem-solving, praise, self-monitoring, assertiveness communication, triggers, relaxation, social support networking, positive activities/alternatives, setting up rewards, positive self-talk, monitoring (by coaches), emotional regulation, relapse prevention, modeling/role-play, and referrals. The content domains are daily living (housing, food, and employment), social relationships, sexual behaviors, PrEP/PEP use, anxiety, depression, other mental health, substance abuse, physical health, violence, and crisis support. Training modules and monitoring tools are based on these practice elements and content domains.

After every contact with a participant, whether a full coaching session or brief navigation interaction or follow-up, the coach completes a brief interaction log or monitoring log using the CommCare mobile-Web app on smartphones, tablets, or Web-connected computers. The log forms record the practice elements used and content domains covered during the interaction. This activity logging functions to prompt coaches to use the skills and address the content priorities of the intervention while simultaneously providing fidelity monitoring to inform supervision and for data analyses.

##### Training and Supervision

Coaches are near-peer, bachelor’s-level paraprofessionals and of similar age, ethnicity, gender, and sexual identity to the participant populations. In addition to the components of the strengths-based model, practice elements, and content areas outlined above, coaches are taught the foundational theory of behavior change (people change slowly over time with small steps and with opportunities and rewards), the shared principles of behavior change (Be Prepared; Act on facts, not feelings). Coaches participate in weekly, cross-site supervision via in-person and videoconference meetings to debrief and jointly problem-solve logistical and clinical challenges with the principal investigator and supervisors. The practice elements are reviewed and reiterated during weekly training and learning community calls with all coaches as their toolbox for addressing the core content areas to be addressed. In both Los Angeles and New Orleans, there are local, on-call clinical psychologists for participants in crisis and who also provide weekly clinical supervision and ongoing booster training to coaches.

#### Condition D/Arm 4: Automated Text-Messaging and Monitoring and Peer Support Via Social Media and Coaching Automated Text-Messaging and Monitoring

This intervention condition delivers the combination of the above interventions, which enables estimation of the cumulative or synergistic effects of what might be considered an ideal model of support for high-risk seronegative youth to optimize their engagement and retention in the HIV prevention continuum.

##### Data Analysis

Analyses are described according to each of the study aims.

###### Aim 1: To Assess the Independent and Synergistic Effects of the Interventions on the HIV Prevention Continuum Outcomes

Multilevel models (MLMs) will be used to test the impact of the intervention on HIV prevention continuum indicators and secondary outcomes over time shown in Textbox 1 in the Background section. MLMs are needed to account for the hierarchical nature of the data and model correlations between repeated observations to properly estimate standard errors on regression coefficients. MLMs are flexible in handling discrete outcomes, such as binary HIV-prevention-continuum indicators (yes/no) and continuous outcomes, such as mental health measures. The MLM analyses will contain main effects for peer support (PEER_i_) and coaching (COACH_i_), as well as a 2-way interaction between peer support and coaching compared with AMM alone. This model parameterization will allow us to test independent effects of peer support and coaching and their synergistic effects on outcomes. MLMs contain interactions between TIME and intervention effects to test for changes in outcome levels between intervention arms over time (our primary goal). Equation 1 shows a random intercept (RI) model that will provide a starting point in the modeling process. Let Y_it_ be an outcome for person i at time point t and let η_it_ be a link function for outcome Y_it_, such as a logit link for binary prevention-continuum indicators. An MLM with a random effect λ_i_ to capture correlations between repeated observations for each person is expressed as:

η_it_ = β_0_ + β_1_ PEER_i_ + β_2_ COACH_i_ + β_3_ TIME_it_ + β_4_(PEER_i_ x TIME_it_) + β_5_(COACH_i_ x TIME_it_) + β_6_(PEER_i_ x COACH_i_ x TIME_it_) + λ_i_. (1)

We will also fit MLM with other covariance structures that we have used in previous HIV intervention studies, including RI and slope (RIAS) and autoregressive covariance structures. The covariance structure with the best fit statistics will be selected. Covariates for demographics and other background characteristics may need to be added to Equation (1) if imbalances are found across intervention arms at baseline.

As a first step, MLM will be fit to each primary outcome and secondary outcome and intervention effects for each outcome will be evaluated separately. We will also evaluate the overall impact of the intervention across binary indicators for optimization of the prevention continuum utilizing a strategy employed by this team to analyze multiple outcomes with one overall statistic, to reflect if there is an overall impact on multiple binary outcomes [111]. Analysis of multiple outcomes through separate regressions increases the probability of finding a significant intervention effect by chance (ie, type I error is inflated). Therefore, we will properly adjust the type I error by conducting simulation studies to determine how many significant intervention effects are needed to declare an effective intervention. Simulation studies assume binary outcomes to be correlated to model a real-world phenomenon.

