##### Sample Size Calculations

Sample size calculations are conducted to detect changes in the probability of an HIV care continuum yes-no indicator, such as PrEP adherence, STI treatment, and 100% condom usage, over 7 time points (every 4 months over 2 years) for the MSM/transgender sample. Calculations show that we have at least 80% power to detect differences in the probability of an indicator as small as 10% to 16% at the last time point between 2 arms with 220 participants at 70% retention. Sample size calculations were conducted through simulation using the following steps. *First*, binary indicator values were simulated from a binomial distribution with the probability of an event (yes) on the basis of an MLM similar to Equation 1. Simulation regression coefficients were specified with baseline rates of 20%, 50%, and 80% to cover a range of care continuum rates we have encountered in previous HIV research and were set to be the same between intervention arms. We specified normally distributed random effects as we did in Equation 1 with an SD of 1.5, similar to what we have found in other studies. Finally, we assumed 30% loss to follow-up and used a sample size of 160 in each arm in simulations. In practice, we anticipated a much lower attrition rate but wanted to be conservative in our sample size calculations. We simulated 1000 datasets for each of the baseline testing rates we specified and for different sample sizes for 2-arm comparisons. *Second*, we fit MLM models to each of the 1000 simulated datasets for differing combinations of parameters. *Finally*, power was estimated to be the ratio of the number of MLM with a significant difference between intervention arms over time divided by 1000. In the end, exploratory analyses will be conducted using the same analysis plan outlined above for 12-month follow-up that includes the cisgender-heterosexual participants.

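### The Aim 1 model has no coach level, so the standard error of COACH x TIME is too small if coaches differ in their effect

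*Protocol article*

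**What the plan says.** The Aim 1 section of the Protocol article justifies multilevel models by the need to "model correlations between repeated observations to properly estimate standard errors on regression coefficients". It introduces the equation with "An MLM with a random effect λ_i_ to capture correlations between repeated observations for each person is expressed as". That person effect is the only random term. The article adds that "Equation 1 shows a random intercept (RI) model that will provide a starting point in the modeling process" and that other covariance structures will be tried, "including RI and slope (RIAS) and autoregressive covariance structures". The structure with the best fit will be kept. No coach level appears in the Data Analysis or Sample Size sections.

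The Condition C/Arm 3 section describes one-to-one work: "The coach and youth identify a primary goal to address following the session". It stresses that "this is not a manualized or scripted intervention". After each contact "the coach completes a brief interaction log or monitoring log". Arm 4 receives the same coaching plus peer support. Arm 1 receives none.

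The Sample Size Calculations section follows the same structure: "We specified normally distributed random effects as we did in Equation 1 with an SD of 1.5". It reports at least 80% power for differences of 10% to 16% between two arms of 220 at 70% retention.

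**The concern.** Arms 3 and 4 hold 2 x 270 = 540 youth, so each coach almost certainly works with many of them. Coaches are free in what they deliver, so youth who share a coach may improve, or fail to improve, together. A random slope or an autoregressive term describes correlation among one person's visits. Neither describes correlation between different youth with the same coach. The design is therefore partially nested: clustered in the coached arms, independent in arm 1.

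The article names change between arms over time as its primary goal and expects the largest effect from coaching. If coach variation is ignored, that comparison gets an interval that is too narrow and a false-positive rate above nominal.

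**Working it through.** **Reproducing the plan's own figure.** Inputs from Sample Size Calculations: 160 per arm, 7 time points, person SD 1.5, and baseline rates of 20%, 50% and 80%, equal between arms. Two-sided 0.05 is assumed, since alpha is not stated. A logistic random-intercept model with independent participants, tested on arm x time without an arm main effect, detects 13.8, 16.3 and 9.6 points with 80% power. This matches the stated 10% to 16% and leaves no allowance for coaches.

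**Two-arm check of the error rate.** From the article: 220 x 0.70 = 154 analysed in the coached arm. Assumed: K = 6 to 12 coaches and ICC 0.01 to 0.05. Controls are n_c = 154, or 690 x (220/270) x 0.70 ≈ 393 if arm 1 has the same share of MSM and transgender youth as the other arms (its share is not stated).

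- m = 154/K; DE = 1 + (m − 1) x ICC
- R = (1/n_c + DE/154) / (1/n_c + 1/154)
- True error of the test as planned = 2 x [1 − Φ(1.96/√R)]
- Power of a clustering-adjusted test = Φ(z/√R − 1.96). Here z = 2.80 for 154 v 154 (80% if independent). For 393 v 154, z = 2.80 x √[(2/154)/(1/393 + 1/154)] = 3.36 (92% if independent).

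Example, 6 coaches and ICC 0.05: m = 25.67; DE = 1 + 24.67 x 0.05 = 2.23; R = (1 + 2.23)/2 = 1.62; √R = 1.27; error = 2 x [1 − Φ(1.54)] = 12.3%; adjusted power = Φ(2.80/1.27 − 1.96) = 60%.

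| Coaches | ICC | DE | Error, n_c 154 | Adjusted power, n_c 154 | Error, n_c 393 | Adjusted power, n_c 393 |
|---|---|---|---|---|---|---|
| 12 | 0.01 | 1.12 | 5.7% | 78% | 6.0% | 90% |
| 8 | 0.02 | 1.37 | 7.2% | 73% | 8.1% | 85% |
| 6 | 0.02 | 1.49 | 7.9% | 71% | 9.2% | 82% |
| 12 | 0.05 | 1.59 | 8.5% | 69% | 10.1% | 80% |
| 8 | 0.05 | 1.91 | 10.4% | 64% | 12.8% | 74% |
| 6 | 0.05 | 2.23 | 12.3% | 60% | 15.4% | 69% |

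These powers use a normal critical value; small-sample degrees of freedom would lower them further. The test as planned, without adjustment, has power Φ((2.80 − 1.96)/√R), which is 79% down to 75% over the same range with equal arms.

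**Check in the longitudinal model.** Add a coach slope in the coached arm only: Var = V + τ²/K, with τ = √[ICC/(1 − ICC) x (1.5² + π²/3)]/6. At 50% baseline V = 0.0404² = 0.00163. With 8 coaches and ICC 0.02, τ = 0.056, τ²/8 = 0.00039 and the variance factor is 1.24. Calculated error is 7.9% and simulated error 7.5%. With ICC 0.05 the factor is 1.62; the simulated SD is 0.051 against a mean model standard error of 0.040, and simulated error is 12%.

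**The interaction.** PEER x COACH x TIME is (arm 4 − arm 3) − (arm 2 − arm 1) in change over time. If the same coaches serve arms 3 and 4 in similar proportions, their additive effects cancel. At ICC 0.05, R = (2 x 0.95 + 2)/4 = 0.975 and the error is 4.7% (4.6% by simulation). With six separate coaches per arm, R = (2 x 2.23 + 2)/4 = 1.62, and the error is 12.3%.

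**The case against.** Equation 1 is offered as a starting point and the list of alternatives is open, so a coach term could be added in the full protocol or analysis plan, which is not shown. This has some weight. However, the article does not simply stay silent: it writes out the model, names the alternatives and the selection rule, claims proper standard errors, and reports power already simulated on that basis. Every structure it names is within person, and nothing points to coaches.

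Shared practice elements, common training, log-based monitoring and weekly cross-site supervision should limit differences between coaches. That is a reason to expect an ICC near the lower end, where the effect is small (5.7% error), not a reason to assume zero.

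Three stronger readings are tempting, and the document does not support them:

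- A reader might infer that the interaction's standard error fails too. With coaches shared across arms 3 and 4 and additive effects, it does not.
- A reader might infer that the planned 80% power is really 60%. The 60% belongs to a test that allows for coaches; the planned test keeps about 75% to 79%, but at an inflated error rate. The power statement also covers comparisons without individual coaching, such as arm 2 with arm 1. For arm 3 with arm 1, the larger arm 1 may make up most of the loss.
- A reader might infer that coach identity is already in the data. The article says the logs record practice elements and content domains; it does not say they identify the coach.

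**Conclusion.** The point holds for COACH x TIME and for other contrasts of a coached arm with an uncoached one. As written, the model cannot deliver proper standard errors for these if coaches differ in their effect on change over time. The direction follows from any positive between-coach variance. The size rests on assumed coach numbers and ICCs: about 6% to 12% true error with 154 per arm, and up to about 15% with about 393 controls. A larger arm 1 helps power but does not correct the error rate. The stated 80% power assumes no coach clustering. It is too favourable for coached comparisons at 154 per arm. With about 393 controls, adjusted power falls below 80% only at ICC 0.05 with 6 or 8 coaches, so the document does not show that the coaching comparison is underpowered. This should be corrected before analysis; confidence in its practical size is medium.

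**What to change.** Add to the Aim 1 model a partially nested coach-level random intercept and TIME slope, active only when COACH = 1, with a coach who serves both arms 3 and 4 treated as the same coach. Use small-sample degrees of freedom or a coach-level bootstrap for the coaching terms. Link each youth to the first coach through the contact logs or assignment records, after confirming that these identify the coach.

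In Sample Size Calculations, state that the 80% figure assumes no coach clustering, and restate power for coached versus uncoached comparisons over a range of ICCs and coach numbers, using the expected number of analysed arm 1 participants.

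The cost is analysis work, a check of the records, and somewhat wider intervals for the coaching effects. If coach variance proves negligible, the estimates will change little.
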